#### Neurotic electrophysiology outcomes

Transcranial magnetic stimulation of motor evoked potential (TMS-MEP) examination will be used for neurotic electrophysiology. Cortical magnetic stimulation will be performed using the Keypoint evoked potential instrument and the magnetic stimulator MagII PR030 with standard circular coil and single puls form. The subjects assume a calm supine or seated position. The compound action potentials of the hand muscle (abductor pollicis brevis) will be recorded using a magnetic stimulator center at 175 px on both sides in the C3 and C4 areas, as well as a spinal cord stimulation center in the C7 area. Simultaneously, the compound action potential of the lower extremity muscle (tibialis anterior) will be recorded, with the coil center situated between 2 and 150 px in front of the CZ region. The intensity of the stimulus should gradually increase from low to 65–75% of the maximum output intensity on the scalp and 65–80% of the maximum output intensity on the lower limbs. Varying limbs can be stimulated at different positions and angles depending on the subject's condition. In order to establish the strong repeatability of compound muscle action potential (CMAP) waves, the complete inspection should measure 4–5 CMAP waves. The highest amplitude, shortest latency, and clearest waveform should be recorded.

The cortical region's amplitude (AMP), potential latency (PL), and central motor conduction time (CMCT) serve as the main markers of TMS-MEP. The outcomes can be categorized into 4 levels: (1) no MEP wave with strong repeatability and a clear and stable waveform is evoked during cortical stimulation; (2) prolonged PL in cortical stimulation; (3) prolongation of CMCT; (4) AMP in the affected side drops by more than half when compared to the healthy side. The last three are categorized as prolonged in this study and will be treated as aberrant MEP.

#### Safety outcomes

The incidence of adverse events, primarily fainting, bent needle, and subcutaneous hematoma during ocular acupuncture, tinnitus, chest tightness, palpitation produced by fMRI scanning noise, and muscle soreness or weariness induced by excessive exercise training, will be recorded for safety evaluation.

### Participant timeline

All participants are scheduled to finish the trial by December 2023 once recruitment and data collecting start in Aug 2022. Enrollment, interventions, and participant assessments are depicted in a temporal schematic diagram (Figure 3).

**Figure 3 F3:**
[figure not shown]
Time schematic diagram of enrolment, interventions, and assessments.

### Sample size

This is a central-peripheral coupling mechanism study rather than a clinical trial. As human-based neuroimaging mechanism studies differ from clinical trials, sample size cannot be estimated using clinical trial computational methods. According to the sample size calculation of imaging studies at home and abroad (47), the sample size is usually 6–12 cases in each group. We determined the sample size as 15 cases per group in accordance with the minimum statistical requirements, considering the drop-out that could be brought on by subjects' compliance and removing the scenario that patients' excessive head movement might influence the data in the statistical analysis progress during fMRI scanning. To keep the statistical results accurate and reliable, 45 healthy controls must be matched simultaneously. In total, 90 subjects-−15 in the OAKT group, 15 in the OA group, 15 in the KT group, and 45 in the HC group—are required for this study.

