## Methods

### Study setting

This is a prospective functional neuroimaging and neurotic electrophysiological study with a case-control design between the PSD with the HC groups and a randomized controlled design within the 3 PSD groups (OAKT group, ocular acupuncture group, and kinesitherapy group). Using fMRI scanning and the TMS-MEP technique, we will assess the central-peripheral neuronal function changes of PSD as well as the coupling effects of OAKT on them. This trial was authorized by the Institutional Review Board of Chengdu University of Traditional Chinese Medicine in April 2022 (reference number: 2022KL-027) and registered (ChiCTR2200060483) at the Chinese Clinical Trial Registry in June 2022. We plan to enroll 90 participants at the Hospital of Chengdu University of Traditional Chinese Medicine from Aug 31, 2022, to Dec 31, 2023. All eligible subjects will be evaluated by fMRI scanning, TMS-MEP examination, and the MMT and Fugl-Mayer assessment following enrollment and on the last day after 4-weeks of waiting (for HC subjects) or intervention (ocular acupuncture, kinesitherapy, or OAKT for PSD subjects, respectively). MMT and Fugl-Meyer score, ReHo value, cluster size, active or positive brain regions and their MNI coordinates, amplitude (AMP), potential latency (PL), and central motor conduction time (CMCT) in the cortical region will be measured, and Pearson correlation analysis will be performed to assess the relationship between clinical and imaging outcomes. This trial will be conducted in accordance with the Standard Protocol Items: Recommendations for Interventional Trials (SPIRIT) (43). Figure 1 displays a flow diagram.

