### Subjects

Patients with post-stroke dyskinesia (PSD) and healthy controls (HC) from the hospital of Chengdu University of Traditional Chinese Medicine and social recruitment, respectively, served as the study's subjects. The diagnostic criteria for patients in this study are based on the Chinese Guidelines for Diagnosis and Treatment of Acute Intracerebral Hemorrhage 2019 (44) and the Chinese Guidelines for Diagnosis and Treatment of Acute Ischemic Stroke 2018 (45). During the anticipated enrollment period from Aug 31, 2022, to December 31, 2023, patients matching the diagnosis standards and satisfying the inclusion and exclusion criteria will be recruited for the study. Table 1 lists the stroke diagnostic criteria.

**Table 1 T1:** Diagnostic criteria of stroke.

**Ischemic stroke**	1. Acute onset
	2. Usually focal or sometimes complete neurologic impairment (unilateral facial or body weakness or numbness, language barriers, and so on)
	3. Imaging lesions or symptoms/signs lasting more than 24 h
	4. Exclude non-vascular etiology
	5. Exclude cerebral hemorrhage by brain CT/MRI scanner
**Hemorrhagic stroke**	1. Acute onset
	2. Usually focal or sometimes complete neurologic impairment accompanied with headache, vomiting, elevated blood pressure, and different degrees of consciousness disorders
	3. Brain CT/MRI scanner showed hemorrhagic focus
	4. Exclude non-vascular etiology.

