### PSD participants

This study will exclude dyskinesia brought on by progressive supranuclear palsy, hepatolenticular degeneration, essential tremor, multiple system atrophy, chorea, tossing syndrome, myoclonus, dystonia, Tourette syndrome, and other conditions.

PSD participants that meet the following criteria: (1) have unilateral dyskinesia and a fresh stroke diagnosis; (2) are right-handed and aged 30–80; (3) have no fMRI or TMS contraindications, and no metallic objects inside the body; (4) haven't undergone acupuncture or exercise therapy for a disease-related condition in the previous month; (5) comprehend and agree with the relevant research content and volunteer to sign the informed consent form can be included in this study. While those who (1) have serious illnesses like uncontrollable hypertension, arrhythmia, serious coronary heart disease, uncontrolled diabetes complications, epilepsy, serious organ failure, and a second stroke, etc.; (2) have unstable vital signs; (3) are vulnerable to co-infection, bleeding, tumor, pregnant women, and postoperative dysfunction; (4) receive other Traditional Chinese Medicine rehabilitation interventions besides acupuncture during treatment; (5) with linguistic or cognitive impairment; (6) with a history of mental illness or long-term sedative use; (7) with conditions that prevent exercise will be excluded.

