### Healthy controls

Healthy controls that satisfy the requirements: (1) have no history of stroke or impaired motor function; (2) are right-handed between the ages of 30 and 80; (3) have no metallic objects in their bodies and no fMRI or TMS contraindications; (4) have not undergone disease-related acupuncture or exercise therapy in the previous month; (5) understand and agree with relevant research content and volunteer to sign the informed consent form can be included in this study.

While those (1) with significant conditions, such as uncontrollable hypertension, arrhythmia, major coronary heart disease, or diabetes complications are not well-controlled, or have epilepsy, serious organ failure, and second attack of stroke, etc.; (2) with unstable vital signs; (3) are susceptible to co-infection, hemorrhage, tumor, pregnant women, postoperative dysfunction patients; (4) get other Traditional Chinese Medicine rehabilitation intervention other than acupuncture during the waiting period; (5) with linguistic or cognitive impairment; (6) with a history of mental illness or long-term sedative use; (7) with conditions that prevent exercise will be excluded.

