#### Correlation analysis between clinical and imaging data

The MATLAB software will be used to conduct the correlation analysis between ReHo values and clinical indexes of PSD. Gender, age, and course will be included as covariates in a Pearson correlation study between the MMT score, Fugl-Meyer score, and ReHo values of PSD. The statistical threshold of *P* < 0.05 will be considered statistically significant.

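### Healthy controls are called matched but no matching factor is named, and the stated group test does not adjust, so the PSD–HC contrast in MEP measures is open to confounding, mainly by age

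*Protocol article*

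**What the plan says.** All references are to the Protocol article.

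- **Design.** Study setting describes a "case-control design between the PSD with the HC groups" alongside the randomised comparison of the three PSD groups.
- **Numbers and matching.** Sample size requires "15 in the OAKT group, 15 in the OA group, 15 in the KT group, and 45 in the HC group" and states: "To keep the statistical results accurate and reliable, 45 healthy controls must be matched simultaneously". No matching variable, tolerance or procedure follows.
- **Eligibility.** Patients "are right-handed and aged 30–80"; controls "are right-handed between the ages of 30 and 80". Controls must also "have no history of stroke or impaired motor function" and meet further criteria on metal, scanner and TMS contraindications, serious illness and cognition. None of these refers to sex or to a patient's age.
- **Source.** Under Subjects, patients and controls come "from the hospital of Chengdu University of Traditional Chinese Medicine and social recruitment, respectively".
- **Group test.** Clinical and electrophysiological data analysis specifies a t-test or ANOVA for normally distributed measures, a non-parametric test otherwise, and chi-square for counts, at two-sided 0.05. No covariate and no matched analysis is mentioned.
- **Imaging test.** Neuroimaging data analysis names only paired t-tests on ReHo.
- **Covariates.** They appear once, in the correlation of ReHo with clinical scores within PSD: "Gender, age, and course will be included as covariates in a Pearson correlation study".

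**The concern.** The case-control part takes half the sample and is meant to show what is abnormal in PSD. Nothing is randomised between PSD and HC, so only the selection of controls or the analysis can separate the effect of stroke from differences in who was recruited.

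The article calls the controls matched and rests the reliability of the results on this. The rules it prints secure equal numbers and a common 50-year age window, and the printed test uses neither matching nor covariates. The authors regard age and gender as relevant enough to adjust for within PSD, yet they do not carry them into the comparison where the two groups have different sources.

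If hospital stroke patients and socially recruited volunteers differ in mean age, any age-related difference in MEP latency, amplitude or CMCT would be read as a PSD abnormality.

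**Working it through.** **1. The plan's own figure.** 3 × 15 + 45 = 90, as stated. The total is not in question.

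**2. Which comparisons are exposed.**

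| Comparison | Test stated | Exposed? |
|---|---|---|
| OAKT v OA v KT | ANOVA or alternative | No, randomised |
| Pre v post within group | Paired t-test for ReHo | No, same person |
| PSD v HC, MEP measures | t-test/ANOVA or alternative, no covariates | Yes |
| PSD v HC, ReHo | None stated | Cannot be judged |

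**3. Size, by illustration.** The documents give no age distribution and no age–outcome association, so every input here except the group sizes and alpha is an assumption.

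- From the article: 45 v 45, two-sided alpha 0.05, hence 88 degrees of freedom.
- Assumed: no stroke effect; mean age gap D; within-group age SD s; correlation r between age and the outcome.
- Shift in outcome SD units: b = r × D / s.
- Noncentrality of the t-test: b / √(2/45) = b × 4.743.

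With s = 12 and r = 0.3:

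| D (years) | b = 0.3 × D / 12 | Noncentrality | Unadjusted, formula | Unadjusted, simulated | Age as covariate, simulated |
|---|---|---|---|---|---|
| 0 | 0 | 0 | 5% | 5.1% | 4.9% |
| 5 | 0.125 | 0.59 | 9.0% | 8.9% | 5.0% |
| 10 | 0.250 | 1.19 | 21.6% | 21.7% | 4.7% |
| 15 | 0.375 | 1.78 | 42.1% | 41.4% | 5.5% |

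The simulation used 8,000 runs per row. Its outcome is linear in age, which favours the covariate model.

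**4. Sensitivity.** With s from 10 to 12 and r from 0.2 to 0.5, the unadjusted rate is 7% to 22% at a 5-year gap, 12% to 65% at 10 years and 22% to 94% at 15 years.

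**5. Sex.** Assume a difference of 10 to 20 percentage points in the share of men and a sex effect of 0.3 to 0.5 SD. The shift is then 0.10 × 0.3 = 0.03 to 0.20 × 0.5 = 0.10 SD, and the rate is 5.2% to 7.6%. On these figures sex matters far less than age.

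**The case against.** **Matching is a sampling procedure, not an eligibility criterion.** Its absence from the criteria contradicts nothing, and an article may leave matching factors to the full protocol. This stands: undefined matching alone would be a request for clarification. If controls are in fact closely matched on age and sex, most of the bias disappears. However, the article does print the group test and does say where covariates enter. The test it prints is the weaker choice for a non-randomised contrast, and that does not depend on what was left out.

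**The imbalance is conjecture.** This also stands. A reader might infer that age and sex are confounded with stroke in this study. The documents do not support that, because they give no distribution for either group; they show only that neither factor is controlled in the stated analysis. Nor is control entry open to any right-handed adult in the age range, since several health criteria also apply. Those criteria simply do not align age or sex.

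**The illustration assumes no stroke effect, although patients are selected for a motor deficit.** True. If stroke does affect the measure, the consequence is a biased estimate rather than a false positive, and the shift b is the same. The highest rates also need large gaps: with s = 12 and r = 0.3, a shift of 0.5 SD requires 0.5 × 12 / 0.3 = 20 years.

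**Part of the MEP assessment is within person.** One abnormality category compares amplitude on the affected and healthy sides, which holds age and sex constant. That protects this category, but not between-group comparisons of amplitude, latency or CMCT values.

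**ReHo.** A reader might extend the criticism to a ReHo contrast between PSD and HC. The paired t-tests appear to be before–after, so that contrast has no stated test; it cannot be called unadjusted.

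**Conclusion.** The point holds in a limited form. The article relies on matched controls without saying on what, and its stated test for clinical and MEP data would not remove an age or sex difference between PSD and HC. The contrast in MEP latency, amplitude and CMCT is therefore open to confounding, chiefly by age.

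The error rates in the working show how sensitive the test is under assumed inputs; they do not estimate what will happen in this study. With no imbalance the rate is the nominal 5%. The randomised treatment comparison is untouched. The change is worth making because adjustment costs almost nothing and the variables are already needed for the correlation analysis.

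**What to change.** - **Clinical and electrophysiological data analysis:** make the PSD–HC comparison an analysis adjusted for age and sex (ANCOVA, or a corresponding regression where the measure is not suited to it). Use the same covariates in any PSD–HC comparison of ReHo.
- **Sample size:** name age and sex as the factors on which controls are frequency-matched to the PSD group as it accrues. Matching keeps the age distributions overlapping, so that the adjustment does not rest on extrapolation.

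**Cost:** revised wording, a running tally of age and sex at control screening, slightly slower control recruitment and minor extra analysis. N stays at 90 and no procedure is added. If controls are already enrolled, the adjusted analysis can still be adopted.

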### Recruitment

All participants are scheduled to finish the trial by December 2023 once recruitment and data collecting start in Aug 2022. Participants who meet the inclusion and exclusion criteria will be recruited after signing an informed consent form prior to the trial. They are free to decide whether or not to take part in the study. Subjects have the option to refuse or withdraw from the study at any time during the procedure. The DMC or researchers may suspend subjects' participation in the study at any time for their good.

### Statistical methods

Only subjects with complete data after 4 weeks of intervention or waiting and pre-post evaluation will be statistically analyzed.

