### Interventions

PSD participants will be randomized to the ocular acupuncture (OA) group, the kinesitherapy (KT) group, or the OAKT group after enrollment.

Subjects in the OAKT group will undergo kinesitherapy after receiving ocular acupuncture stimulation at the “Upper-Jiao Area” (ACU 1), “Lower-Jiao Area” (ACU 2), “Liver Area” (ACU 3), and “Kidney Area” (ACU 4) (16) (Figure 2). This involves a series of advised exercise training consisting of warm-up exercises (low levels of aerobic exercise), exercise training (including aerobic training, walking training, treadmill training, resistance training, upper limb flexion adduction-abduction exercise, lower extremity knee flexion-extension exercise, flexibility training), and relaxation training (stretching exercise) (46). Needles for ocular acupuncture will remain embedded until the day's exercise training is finished. OAKT will be manipulated once a day, 5 days a week, for 4 weeks, with 2 days off between courses. Sweating, breathing, pulse, and blood pressure measures will be used to adjust the exercise prescription.

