#### Functional neuroimaging outcomes

A 3.0 Tesla high-field full-body magnetic resonance imaging system will be used for functional neuroimaging. Bold-fMRI data is acquired in the resting state following structural image scanning with a three-dimensional fast-spoiled gradient-recalled sequence and functional image scanning with a Gradient-Echo-Planar Imaging for 10 min, covering the entire brain, cerebellum, and brain stem. The parameters for scanning structural images include layer a thickness of 1 mm, a Repetition Time/Echo Time (TR/TE) of 2,700 ms/3.39 ms, Field of Vision (FOV) of 256 mm^2^, Matrix of 256 × 256, a Flip Angle of 7°, and an in-plane resolution of 1 × 1 mm. The settings for functional image scanning include a slice thickness of 5 mm, a TR/TE of 2,000 ms/30 ms, Matrix of 64 x 64, FOV of 240 mm^2^, and a Flip Angle of 90°.

The original fMRI data in DICOM format will be copied to a computer and converted by MRIcro software into an analyzable.img file format. The software packages Data Processing Assistant for Resting-State fMRI (DPARSF) and the statistical parametric mapping software package (SPM12) in Matlab (Mathworks, Inc., Natick, Massachusetts) will be utilized to preprocess the fMRI data. Preprocessing steps include (1) realign, all images of each selected subject whose translation in all directions (x, y, z) is <1 mm and rotation angle is <1 degree will be aligned with its first image for further analysis; (2) Spatial normalization, registers images of all subjects to the standard template of Montreal Neurological Institute (MNI) neurological spatial coordinates and re-cuts the voxel to 3 mm 3 for data standardization and individual comparability; (3) slice-timing correction, uses a mathematical approach to collect all images at the same time point by default, with the intermediate time point as the reference layer; (4) smoothing with an 8 mm full width at half maximum (FWHM) kernel to reduce spatial noise, as well as errors caused by spatial normalization; (5) Detrending with linear regression and filtering with a frequency window of 0.01–0.08 Hz to remove low frequency noise caused by respiration, heartbeat, and other physiological factors, as well as high frequency noise from the MRI scanner itself.

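### Limiting every analysis to subjects with complete pre-post data can bias the randomised comparison of the three PSD arms and, read literally, discards valid clinical scores

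*Protocol article*

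**What the plan says.** Statistical methods, ahead of the clinical and electrophysiological, imaging and correlation subsections, states: "Only subjects with complete data after 4 weeks of intervention or waiting and pre-post evaluation will be statistically analyzed". No analysis of all randomised patients, outcome-specific set or missing-data method stands beside it.

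The rule covers a randomised comparison: "PSD participants will be randomized to the ocular acupuncture (OA) group, the kinesitherapy (KT) group, or the OAKT group after enrollment" (Interventions). Study setting also describes the design within the PSD patients as randomised and controlled.

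The document expects losses after allocation. Sample size names poor compliance and excessive head movement as reasons for its margin. Recruitment allows withdrawal at any time, and allows the DMC or researchers to suspend a subject for that subject's benefit. Functional neuroimaging outcomes takes forward images of subjects "whose translation in all directions (x, y, z) is <1 mm and rotation angle is <1 degree". MMT and Fugl-Meyer are measured twice, at baseline and at the end (Clinical outcomes).

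**The concern.** Randomisation makes the three arms comparable as allocated. A rule that selects patients by what happens afterwards keeps that comparability only if the selection is unrelated to outcome, or acts the same way in each arm. The arms differ in burden: needles alone, exercise alone, or both. Tolerance and drop-out may therefore differ between them. Severe stroke could plausibly make head movement or withdrawal more likely. With 15 patients per arm, a few selective losses can move a mean noticeably.

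The second problem needs no assumption about why patients are lost. A patient who finishes treatment and has both Fugl-Meyer and MMT scores, but moves too much in the scanner, does not have complete data in the ordinary sense of those words. The rule as worded then discards observed clinical and MEP results for a reason that belongs to imaging alone.

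**Working it through.** **The plan's own figure.** 3 × 15 + 45 = 90, which reproduces the stated total. The 15 per arm has no formula behind it. The article says "the sample size is usually 6–12 cases in each group" and then "We determined the sample size as 15 cases per group in accordance with the minimum statistical requirements", with a margin for losses but no rate. If 12 were the target, 12/(1 − 0.20) = 15, so 20% loss fits. From 10 or 6, the loss would have to be 1 − 10/15 = 33% or 1 − 6/15 = 60%. The figure of 20% (3 of 15) is therefore an assumption.

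**Precision.** Two-sample t-test, two-sided 0.05 (the article's level), 80% power (assumed), noncentral t:
- 15 per arm: detectable difference 1.06 SD
- 12 per arm: 1.20 SD

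The normal approximation (1.960 + 0.842) × √(2/n) gives 1.02 and 1.14 SD. For a true difference of 1.0 SD, t-test power falls from 75% to 65%.

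**Bias.** Quantity: difference in mean change between two arms among completers, when the true difference is 0. Assumptions: logistic loss with an odds ratio of 2 or 4 per SD; correlation of 0.3 between baseline and change; loss rates as listed. Type I error comes from 40,000 simulated trials with 15 randomised per arm.

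| Assumed loss | Bias (SD) | Type I error |
|---|---|---|
| Unrelated to outcome, 20/20% or 10/30% | 0 | 5.1% |
| Related to change, identical in both arms, 20/20% | 0 | 5.1% |
| Related to baseline severity only, 10/30% | 0.04–0.06 | not run |
| Related to change, 10/30% | 0.12–0.20 | 7.5% (odds ratio 4) |
| 20% each, related to change in one arm only | 0.13–0.22 | 8.1% (odds ratio 4) |
| 20% each, opposite directions in the two arms | 0.26–0.43 | 19% (odds ratio 4) |
| The 3 worst of 15 removed from one arm | 0.33 | not run |

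The large-sample formula for the last row is φ(z_q)/(1 − q). With q = 0.20 it gives 0.280/0.80 = 0.35 SD, close to the 0.33 SD for exactly 3 of 15.

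**What a model on all randomised patients would recover.** There are only two assessments, so a drop-out contributes a baseline value alone. In a simulation of the last row (correlation 0.3, 20,000 runs), the bias was 0.33 SD for completers and 0.30 SD for a mixed model. With 3 of 15 lost at random per arm, the standard errors were 0.410 and 0.408. A mixed model therefore repairs little for patients with no week-4 score. The gain comes from patients who do have week-4 data and would be removed for another reason.

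**The case against.** The article calls this a mechanism study and says "sample size cannot be estimated using clinical trial computational methods". Its ReHo analysis uses paired t-tests, which need complete pairs. For imaging, part of the rule is unavoidable, and this stands. It does not carry over to the clinical and MEP outcomes, which are compared between groups in a design described as randomised.

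The motion limits sit in the fMRI preprocessing steps. The article does not say that a patient who fails them loses the clinical scores. The authors may intend a separate set for each outcome. That is possible, but the sentence does not say so, and its plain meaning is the opposite.

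Four stronger readings are tempting and are not supported:
- **That the rule certainly biases the result, because losses are tied to severity and response.** The article states no such link. Severity is a reasonable inference, and response a weaker one.
- **That a patient without an evocable MEP counts as incomplete.** Neurotic electrophysiology outcomes lists "no MEP wave with strong repeatability and a clear and stable waveform is evoked during cortical stimulation" as the first of four result levels, so it is a recorded finding. Only latency and conduction time are undefined for that patient.
- **That the plan implies losing at least 3 of 15, and hence 0.35 SD.** The range of 6–12 is described as usual, not as required. The 0.35 SD needs the worst responders to leave one arm and none to leave the other.
- **That the fourth exclusion criterion, "receive other Traditional Chinese Medicine rehabilitation interventions besides acupuncture during treatment", removes patients from analysis after allocation.** It can only arise during treatment, but it stands in the eligibility list, and the analysis rule does not invoke it.

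**Conclusion.** The concern holds in a limited form. The article itself fixes a completer population for every analysis, so this is not a detail left to an analysis plan. For the three randomised PSD arms the rule can bias the comparison. Whether it does, and in which direction, cannot be known from the document. The 0–0.4 SD range rests entirely on the assumed loss rates and odds ratios. It is zero under the null if loss is unrelated to outcome or the same in each arm, and the upper end needs extreme or opposite mechanisms. The loss of precision likewise depends on the assumed 3 of 15.

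The discarding of existing MMT, Fugl-Meyer and MEP data after an unusable scan follows from the literal wording and has no analytic justification. The contrast with healthy controls is not randomised, and this point does not extend to it.

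**What to change.** Replace the opening sentence of Statistical methods so that it says:
- Every randomised PSD patient is analysed in the assigned arm, for each outcome on which he or she has data, whatever the adherence or co-intervention after allocation.
- The motion limits apply to the ReHo analysis and its correlations only.
- Absent MEP counts as the result level already defined, not as missing.
- Losses are reported by arm and reason.
- The completer analysis is kept as secondary.
- A delta-adjusted (missing-not-at-random) sensitivity analysis is added for missing week-4 clinical scores. The completer analysis cannot do this job, because it generally rests on equal or stronger assumptions than a missing-at-random model.

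The cost is new wording, modest extra analysis and different patient numbers across outcomes, with no added patients or visits. Precision is recovered only for patients who have week-4 data on the outcome concerned. For true drop-outs, the sensitivity analysis shows how far the result depends on what is missing but does not restore it.
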